### **11.1.4. Analysis of Demographic and Baseline Data**

Descriptive statistics for demographic and pre-treatment subject characteristics will be presented by group. Continuous variables will be analyzed using an independent t-test or Wilcoxon rank sum test depending on normality. Categorical variables will be analyzed using a Chi-square test or Fisher's exact test.

## **11.2. Statistical Analysis of Outcome Measures**

### **11.2.1. Primary Outcome Measures**

Hypothesis: The mean change in the WURSS-21-K total score (symptom score + quality of life score) from baseline to Day 7 is not equal between the test group and the control group.

The analysis will be conducted using an ANCOVA model with the group as the effect and the baseline WURSS-21-K total score as a covariate. If necessary, other variables that show a statistical difference in demographic characteristics or that could affect cold symptoms will also be included as covariates. The least-square mean (LSM) difference between the control and test groups, its 95% confidence interval, and the p-value will be presented.

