#### 2) Rationale

This clinical trial is designed to evaluate the efficacy and safety of GGTCS for patients with nasal congestion due to the common cold. The primary outcome measure is the WRUSS-21-K. The change in the WRUSS-21-K from baseline to Day 7 (after a total of 21 doses, 3 times a day for 7 days) will be compared between the test group (GGTCS) and the control group (placebo).

The hypothesis for this clinical trial is as follows:

[Hypothesis]  $H_0$ (Null Hypothesis):  $\mu_t = \mu_c$  vs.  $H_1$ (Alternative Hypothesis):  $\mu_t \neq \mu_c$

$\mu_t$  : The mean change in the WRUSS-21-K score from baseline to Day 7 in the test group.

$\mu_c$  : The mean change in the WRUSS-21-K score from baseline to Day 7 in the control group.

Table 1. Change in WRUSS-21-K of Eungyo-san, Sams0-eum, placebo between pre- and post-treatment.

|                   | Pre-Treatment | Post-Treatment | Change (Before-After)* |
|-------------------|---------------|----------------|------------------------|
| Eungyo-san (n=44) | 56.28(30.47)  | 13.86(22.43)   | 44.00(22.27)           |
| Sams0-eum (n=42)  | 54.74(30.98)  | 17.05(24.29)   | 40.12(18.78)           |
| Placebo (n=42)    | 66.48(31.64)  | 33.33(30.02)   | 29.09(21.89)           |

\*: Change adjusting WRUSS-21-K score of baseline.

Previous studies (K.-I. Kim, M. Hong) showed that the mean (standard deviation) change in the WRUSS-21-K score from pre- to post-treatment was 29.09 (21.89) for the placebo group, 44.00 (22.27) for the Eungyo-san treatment group, and 40.12 (18.78) for the Samso-eum treatment group. The mean difference in effect was 14.91 for the Eungyo-san treatment group compared with the placebo group, with a pooled standard deviation of 22.09. The mean difference in effect for Samso-eum compared with the placebo group was 11.03, with a pooled standard deviation of 20.39. In this clinical trial, the significance level ( $\alpha$ ) was set at a two-sided 5%, and the power ( $1-\beta$ ) is 80%. Based on the results of the previous studies, the effect difference is set at 10 and the standard deviation at 21. The calculated number of subjects required to confirm the effect of the GGTCS group compared with the placebo group is as follows.

$$\left\{ \frac{2 \left( z_{1-\frac{\alpha}{2}} + z_{\beta} \right)^2 * \sigma^2}{|\mu_T - \mu_c|} \right\} = \left\{ \frac{2(1.96 + 0.84)^2 * 21^2}{10^2} \right\} = 69.227 \approx 70$$

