Based on the 1:1 allocation ratio between the treatment and control groups, the required number of subjects per group is 70. Considering a 20% dropout rate for this clinical trial, a total of 176 subjects (88 per group) are needed.

Subjects will be recruited from multiple centers, with a target of 88 subjects from Daejeon University Daejeon Korean Medicine Hospital, and 44 subjects each from Kyung Hee University Korean Medicine Hospital and Pusan National University Korean Medicine Hospital. However, the number of subjects recruited per center may vary depending on the recruitment speed. The final allocation of subjects per center will be re-evaluated by the Central Data Management (DM) team at the midpoint (50%) of the total study period, based on the recruitment speed of each center. If the number of subjects per center changes, an independent statistician will generate new codes as needed, considering the block size, and these will be reflected in the randomization schedule for each center. Investigational products will be provided to each study site based on their initial number of subjects. Additional products for sites with increased subject numbers will be provided by the drug manufacturer (National Institute of the Korean Medicine Development) according to the newly generated randomization codes. Sites with a reduced subject number will be instructed to discard the remaining randomization codes.

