### 6.3. Randomization

- This clinical trial will use blocked randomization, without stratification.
- A statistician or an independent researcher will use the statistical program SAS® Version 9.4 (SAS Institute Inc., Cary, NC, USA) to generate a predetermined randomization list based on a table of random numbers, and will assign subjects to either the test group or the control group. This list will then be provided to the randomization manager (a pharmaceutical company representative).
- The pharmaceutical company's labeling manager will label the investigational products with unique randomization numbers and deliver them to the institutional pharmacist. To ensure blinding of subjects, investigators, monitors, and pharmacists, the test and placebo drugs will be kept identical in appearance, with only the randomization number on the label. The randomization manager will be an individual independent of the study interventions and assessments, and will not disclose the information until the completion of the clinical trial, unless there are special circumstances.
- The identification codes for each subject on the randomization list will be sealed in a small envelope in advance. The labels will not show any difference between the groups. The allocation list of unique codes will be managed by the unblinding manager of the clinical trial, and will not be disclosed until the study is fully completed, except in cases where access to the code is unavoidable due to a serious adverse event.
- Subjects who meet all inclusion and exclusion criteria will be assigned to either the test group or the control group according to the pre-generated randomization list, starting from the lowest available number. The institutional pharmacist will sequentially supply the investigational products to the subjects based on their assigned identification code numbers.
- An independent statistician will generate randomization codes for each site, incorporating the site code. If the number of subjects per site changes, the independent statistician will generate new codes as needed, considering the block size, and these will be reflected in the randomization list for each site.

(Site codes: Daejeon University Daejeon Korean Medicine Hospital 01, Kyung Hee University Korean Medicine Hospital 02, Pusan National University Korean Medicine Hospital 03)

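### Randomisation is blocked within site, but the primary ANCOVA leaves site out and lets other covariates in by a data-dependent rule; the first costs a little power, the second leaves the primary model unfixed

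*Protocol*

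**What the plan says.** **Randomisation.** Section 6.3 opens with "This clinical trial will use blocked randomization, without stratification". The last item of the same section reads "An independent statistician will generate randomization codes for each site, incorporating the site code", and adds that if site numbers change, new codes are made with the block size in mind and entered in each site's list. Section 5.3 (Rationale) likewise speaks of one schedule per centre, with targets of 88, 44 and 44 subjects. Sites whose target is cut discard their remaining codes.

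**Primary model.** Section 11.2.1: "The analysis will be conducted using an ANCOVA model with the group as the effect and the baseline WURSS-21-K total score as a covariate". The synopsis gives the same two terms. Neither names site.

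**Further covariates.** Section 11.2.1 then provides that, if necessary, "other variables that show a statistical difference in demographic characteristics or that could affect cold symptoms will also be included as covariates". The synopsis has the same two grounds but words them as a permission: such variables may be added. Neither place gives a list, a threshold, a time of decision or a person who decides. Section 11.2.2 applies the primary method to the change-from-baseline secondary outcomes, so the rule carries over to them.

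**The concern.** There are two separate issues.

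1. Separate blocked lists balance the arms within each hospital. That removes site differences from the true variance of the treatment contrast. A model without site still counts them as error, so its standard error is larger than the real sampling variability. At stake is some efficiency and a test that runs below its nominal level.

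2. In a randomised trial, a significant baseline difference is a chance event and says nothing about whether the variable predicts the outcome. A rule that keys on such differences can be run only once the arms are compared. The second ground, possible influence on cold symptoms, has no boundary. Together with the if-necessary condition, it means the single primary test has no fixed model, and several candidate p-values can exist before one is reported.

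**Working it through.** **Plan's own figure.** Inputs from section 5.3: two-sided 5%, power 80%, "the effect difference is set at 10 and the standard deviation at 21", and "Based on the 1:1 allocation ratio between the treatment and control groups, the required number of subjects per group is 70".

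n = 2(1.960 + 0.842)² × 21² / 10² = 69.227, so 70 per group (69.149 with the rounded z-values printed in the formula, also 70). With 20% dropout, 70/0.8 = 87.5, so 88 per group and 176 in all. Power at 70 per group is 80.4%. The sample size reproduces and is not in question.

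**Effect of leaving site out.** Let ρ be the share of residual variance due to site. The protocol does not give it, so a range is shown. With 1:1 balance within site and n = 70 per group:

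- SE reported without site: 21√(2/70) = 3.550
- true SE: 3.550 × √(1−ρ)
- type I error without site: 2[1 − Φ(1.96/√(1−ρ))]
- power without site: Φ[(10 − 1.96 × 3.550)/(3.550√(1−ρ))]
- power with site: Φ[10/(3.550√(1−ρ)) − 1.96]

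For ρ = 0.10 the true SE is 3.368. Type I error is 2[1 − Φ(2.066)] = 3.9%, and power is Φ(0.90) = 81.7% without site against Φ(1.01) = 84.4% with it.

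| ρ (assumed) | Model SE too large by | Type I error, no site | Power, no site | Power, with site |
|---|---|---|---|---|
| 0 | 0% | 5.0% | 80.4% | 80.4% |
| 0.02 | 1.0% | 4.8% | 80.7% | 81.2% |
| 0.05 | 2.6% | 4.4% | 81.0% | 82.4% |
| 0.10 | 5.4% | 3.9% | 81.7% | 84.4% |
| 0.20 | 11.8% | 2.8% | 83.1% | 88.3% |

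Simulation at 88 per group in sites of 88/44/44 (blocks of 4, assumed; 4000 trials) gave type I error of 4.7%, 4.3%, 3.9% and 2.7% at ρ = 0.02, 0.05, 0.10 and 0.20. A run at 70 per group (3000 trials; simulation standard error about √(0.05 × 0.95/3000) = 0.4 points) was noisier: 5.1%, 4.1% and 3.5% at ρ = 0.05, 0.10 and 0.20. At ρ = 0.20 its mean model SE was 3.56 against an empirical SD of 3.23.

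**Effect of the covariate rule.** The protocol gives neither the number nor the strength of candidates. Six independent covariates and no site effect are assumed.

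- Chance that at least one of six differs at 5%: 1 − 0.95⁶ = 26.5%. The rule would often be triggered.
- Imbalance rule applied mechanically: type I error 4.9%, 3.7% and 3.7% when the covariates jointly explain about 6%, 25% and 49% of residual variance. Two further runs with a slope of 0.2 per covariate gave 4.4% and 4.8%. There is no inflation.
- Better p-value of the base model and the imbalance-rule model: 5.4% (5.2% with slopes of 0.1), from 2500 trials. This is barely distinguishable from 5%.
- Smallest p-value among nine models (base, rule-based, six single-covariate, all six): 7.6%, 10.3% and 11.9% at the 6%, 25% and 49% shares.
- Smallest p-value among all 2⁶ = 64 covariate subsets: 12% to 13% with slopes of 0.2, and 8.6% with slopes of 0.1.

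**The case against.** **Site.** The words on stratification may mean only that no patient factor is stratified, with the site lists described separately. Allocation is workable on either reading, so this part is a wording point. The lost power is also modest. At 88 per group and a difference of 10, power without and with site is 88.7% and 89.1% (ρ = 0.02), 89.1% and 90.0% (0.05), and 89.7% and 91.5% (0.10). Site differences in initial severity are partly absorbed by the baseline score already in the model. All of this stands, and it limits the size of the point. It does not remove the mismatch between design and model.

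A reader might infer that a standard error which ignores the design makes the test invalid or raises false positives. The documents do not support that. The error runs the other way, and every setting above stays over the planned 80% power.

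**Covariates.** A reader might also infer that the plan carries a 9% to 12% type I error. It does not. The imbalance rule as written holds the level. Figures in that range need someone to fit many models and report the smallest p-value. The protocol does not prescribe this, though nothing in it excludes it.

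**SAP.** A statistical analysis plan, not seen here, could list the variables thought to affect symptoms, and could include site. Allocation is withheld until the study ends (sections 6.3 and 6.4), so fixing such a list in time is feasible. That would answer the open clause in practice. It would not answer the imbalance clause, which the protocol states as its rule, or the difference between synopsis and body.

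**Conclusion.** The point holds in limited form.

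- Section 6.3 describes stratification by site while denying stratification, and the primary model does not follow the design. At an assumed site share of 2% to 10%, type I error is about 4.8% to 3.9% and power about 0.5 to 3 points lower than it could be. At a zero share there is no loss. This is inefficiency on the conservative side.
- The covariate clause is a defect of specification. It selects on chance differences rather than prognostic value, its second ground is unbounded, and synopsis and body disagree on whether it is optional. Error above 5% (roughly 8% to 13%) arises only under outcome-driven selection, with six assumed covariates. Those are worst cases and not predictions.

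The change should be made because it is nearly free and fixes the primary model in advance. The planned sample size is unaffected.

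**What to change.** - Section 6.3: describe the scheme as blocked randomisation stratified by site.
- Section 11.2.1 and the synopsis: fix the primary model as group, site (fixed factor, three levels) and baseline WURSS-21-K total score, in identical wording.
- Both places: delete the sentence that adds covariates on observed differences or possible influence on symptoms.
- Put any further covariates in a sensitivity analysis, named before unblinding. Section 11.2.2 then inherits the fixed model by reference.

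Cost: protocol wording and two degrees of freedom. No extra patients are needed.

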### **11.2.2. Secondary Outcome Measures**

- 1) The change from baseline to Day 7 in Nasal Congestion Severity Score, Nasal Symptom Score VAS, Systemic Symptom Score VAS, WURSS-21-K symptom and quality of life scores, EQ-5D-5L score, and duration of cold symptoms will be tested using the same method as the primary outcome measures.
- 2) To compare the differences in trend changes between groups, a Repeated Measures Analysis of Variance (RM ANOVA) will be used, with Dunnett's procedure for multiple comparison correction (comparing each time point to baseline).
- 3) The Global Evaluation of Efficacy satisfaction and cold recovery status on Day 7 will be analyzed using a Chi-square test. If the Global Evaluation of Efficacy score is treated as a continuous variable, an Independent t-test or Wilcoxon rank sum test will be performed.

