|                         | 
 
7. Duration of common cold symptoms
 
8. Common cold recovery status on Day 7
 
9. Global Evaluation of Efficacy score on Day 7
 
10. Change in the EQ-5D-5L score from Baseline to Day 7
 
 
• Exploratory Outcome Measures
 
 
1. Change in the WURSS-21-K total score according to the common cold pattern identification (Wind-Cold type, Wind-Heat type, or Other types).
 
                                                                                                                                                                                                                                                                                                                                                                                                                                                                                                                                                                                                                                                                                                                                                                                                                                                                                                                                                                                                                                                                                                                                                                                                                                                                                                                                                                                                                   |

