## 2. Secondary Outcome Measures

- 1) The changes in the following secondary outcome measures from baseline to Day 7 will be tested using the same method as the primary efficacy endpoint: Nasal Congestion Severity Score, Nasal Symptom Score VAS, Systemic Symptom Score VAS, WURSS-21-K symptom score, WURSS-21-K quality of life score, and EQ-5D-5L score. Additionally, the pre- and post-treatment differences within each group will be analyzed using a Student's paired t-test, depending on the normality of the data.
- 2) To compare the differences in trends between the groups, Repeated Measures Analysis of Variance (RM ANOVA) will be used, with Dunnett's procedure for multiple comparisons (comparing each time point against baseline).
- 3) The Global Evaluation of Efficacy satisfaction and cold recovery status at Day 7 will be analyzed using the Chi-square test. However, if the Global Evaluation of Efficacy satisfaction score is treated as a continuous variable, an Independent t-test or Wilcoxon rank-sum test will be performed.

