## 4) Assessments of WURSS-21-K, Nasal Symptom Score VAS, Systemic Symptom Score VAS, EQ-5D-5L

## 5) Assignment of Randomization Number

- Subjects who are deemed eligible for this clinical trial based on the inclusion/exclusion criteria will be assigned a randomization number in the following format, in the order of their enrollment.
- Site codes: Daejeon University Daejeon Korean Medicine Hospital 01, Kyung Hee University Korean Medicine Hospital 02, Pusan National University Korean Medicine Hospital 03

|                              |
|------------------------------|
| ✓ KIOM_2024_CC_GGTCS_0X_R000 |
|------------------------------|

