#### **10.3.2.6.Duration of Cold Symptom**

- Subjects will be asked if all cold-related symptoms have resolved. If they respond that the cold is completely gone, the date of resolution will be confirmed to assess the total duration of symptoms.
- Daily diary distributed at Visit 2 will be used to check for daily symptom resolution, and it will be collected at Visit 3.

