### **11.1.3. Handling of Missing Data**

Missing data will be imputed using the Last Observation Carried Forward (LOCF) method. This method will only be applied to efficacy endpoints in the FAS.

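### Section 11.2.2 analyses duration of cold symptoms as a change from baseline by ANCOVA, with no rule for subjects still ill at the last visit

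*Protocol*

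**What the plan says.** The synopsis lists the seventh of ten secondary outcomes as "Duration of common cold symptoms", a plain duration and not a change.

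Section 11.2.2, item 1, begins "The change from baseline to Day 7 in Nasal Congestion Severity Score" and ends "EQ-5D-5L score, and duration of cold symptoms will be tested using the same method as the primary outcome measures". Section 11.2.1 defines that method as an "ANCOVA model with the group as the effect and the baseline WURSS-21-K total score as a covariate", reported as a least-squares mean difference.

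Section 10.3.2.6 says how duration is obtained: "If they respond that the cold is completely gone, the date of resolution will be confirmed to assess the total duration of symptoms". The baseline items in section 10.2.2 are "Assessments of WURSS-21-K, Nasal Symptom Score VAS, Systemic Symptom Score VAS, EQ-5D-5L"; duration is not among them. The diary instructions in the same section have subjects record duration daily, and section 10.2.3 lists it again at Visit 3 (Day 7-10), the last planned visit.

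The only missing-data rule, in section 11.1.3, is "Missing data will be imputed using the Last Observation Carried Forward (LOCF) method", applied to efficacy endpoints in the FAS. No censoring rule or time-to-event method is given.

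The synopsis version of the item 1 list reads "Nasal Congestion Severity Score, Nasal Symptom Score VAS, Systemic Symptom Score VAS, WURSS-21-K symptom score, WURSS-21-K quality of life score, and EQ-5D-5L score". Duration is absent there, and no other item of the synopsis analysis gives it a method.

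**The concern.** Duration is one elapsed time per subject. It has no value at Day 0 from which to measure change, and for a subject who has not recovered by Visit 3 all that is known is that it exceeds the time observed. An ANCOVA of means has no place for that information.

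The protocol expects such subjects, since recovery at Visit 3 is a separate yes/no outcome (section 10.3.2.7). In the earlier study tabulated in section 5.3, the placebo group still had a mean post-treatment score of 33.33 (SD 30.02). That does not give a recovery rate, but it shows that recovery was not complete.

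The stated rules therefore leave two routes: leave the unrecovered out, or enter elapsed time (the running diary value, or the same value through LOCF) as if the cold had ended. The two give different answers, and the choice would be made after the fact.

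**Working it through.** **The plan's own figure.** The protocol computes nothing for duration. Its one calculation, for the primary outcome, reproduces: 2(z₀.₉₇₅ + z₀.₈₀)² × 21² / 10² = 69.23, so 70 per arm; 70 / 0.8 = 87.5, so 88 per arm and 176 in total. I use 88 per arm below.

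**Assumptions, not in the protocol.** Exponential time to recovery from Day 0; median 9 days on placebo and 6 on GGTCS; everyone followed to T = 7 days; durations rounded up to whole days in the simulation.

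**Closed-form results.** The rate is l = ln 2 / median: 0.0770 (placebo) and 0.1155 (GGTCS), a hazard ratio for recovery of 1.5.

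- Recovered by Day 7, 1 − exp(−lT): 42% and 55%.
- Mean duration among the recovered, 1/l − T/(exp(lT) − 1): 3.19 and 3.03 days, a difference of 0.15 days.
- Restricted mean to Day 7, (1 − exp(−lT))/l: 5.41 and 4.80 days, a difference of 0.61 days.

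The recovered-only comparison thus shows about a quarter (0.15/0.61) of the difference that can be seen within seven days.

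**Simulated power, 88 per arm, two-sided 5%.**

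| Assumed medians (days) | Recovered only, t-test | Unrecovered set to Day 7, t-test | Log-rank with censoring |
|---|---|---|---|
| 9 vs 6 | 6% | 36% | 45% |
| 8 vs 6 | 6% | 23% | 27% |

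Repeat runs move these by one or two percentage points. As a check on the log-rank column, the expected events are 88 × (0.417 + 0.555) = 85.5. The Schoenfeld approximation gives Φ(ln 1.5 × √85.5 / 2 − 1.96) = Φ(−0.09) = 0.47. For 8 vs 6 it gives 0.27.

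**Range over other assumptions.** Weibull durations with shape 1 or 2, hazard ratio 1.5, 88 per arm, followed to Day 7:

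| Placebo recovered by Day 7 (assumed) | Recovered only | Set to Day 7 | Log-rank |
|---|---|---|---|
| 30% | 0.04–0.05 | 0.23–0.26 | 0.35–0.38 |
| 50% | 0.09 | 0.40 | 0.50–0.55 |
| 70% | 0.17 | 0.48–0.59 | 0.61–0.66 |

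With a hazard ratio of 1.0, all three rejected in about 4–7% of runs, so false positives are not inflated.

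**The case against.** Four points on the other side carry weight.

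1. *A value may exist for the still-ill.* The diary collects duration daily and section 10.2.3 lists it at Visit 3, so a running figure for unrecovered subjects is a natural reading. This stands. A reader might infer that these subjects have no value and that LOCF cannot act; the documents do not support that. What LOCF would carry is elapsed time, which counts an ongoing cold as finished.

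2. *The model can be fitted.* Section 11.2.1 names baseline WURSS-21-K total as the covariate. Read literally, the same method gives duration regressed on group and that score, which needs no baseline duration. This stands, so calling the analysis impossible goes too far. The change-from-baseline wording is still wrong, and the covariate does not deal with censoring.

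3. *Dropping the unrecovered is the worse of two routes.* Nothing in the protocol says they are dropped. With everyone followed to one common cut-off, setting them to Day 7 validly estimates the restricted-mean difference, and the power loss is moderate (36% against 45%). This stands for that ideal case. Visit 3 spans Day 7-10 and section 5.3 allows for 20% dropout, so a common cut-off with complete follow-up is not assured.

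4. *The endpoint is secondary.* It is one of ten, and Day 7 recovery has its own Chi-square test, which can count unrecovered subjects. This stands and limits the severity.

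It is also tempting to set the 0.15-day difference against the assumed 3-day gap in medians. That compares a mean within seven days with an unrestricted median; 0.61 days is the fair comparator.

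**Conclusion.** The concern holds as a should-fix. Section 11.2.2 states an unsuitable method for duration; it does not merely leave detail open. It treats as a change something that has no baseline, gives no rule for subjects censored at the last visit, and disagrees with the synopsis.

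The consequence is attenuation and lost power on one secondary endpoint. In the main assumed scenario power falls from about 45% to 36% or to 6%, depending on which route the analyst takes. These sizes rest on assumed recovery distributions and on complete follow-up to Day 7. The direction, towards no effect, applies to censoring at the end of follow-up; unequal early dropout between arms could push the result either way. The primary analysis and the sample size are untouched.

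**What to change.** - Remove duration from section 11.2.2, item 1.
- Define the endpoint as time from first dose to the first diary day marked completely resolved. First dose is the safer origin: section 10.3.2.6 speaks of total duration, but no listed case report form item explicitly records an onset date.
- Censor unresolved subjects at their last diary entry or Visit 3.
- Use Kaplan-Meier curves with a log-rank test, or a Cox model adjusted for baseline WURSS-21-K total. Stratifying by site is optional; the primary model does not use site.
- State that LOCF does not apply to this endpoint.
- Add a sensitivity analysis that keeps subjects withdrawn for worsening (section 7.1, item 5) as unresolved to the end of follow-up, because censoring them may be informative.
- Give the same method in the synopsis and in section 11.2.2.

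The cost is a wording amendment. With first dose as the origin, the diary and dosing records already in the plan suffice, and no visit, form or subject is added.

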| Efficacy Outcome Measures          | 
 
• Primary Outcome Measures 
 
1. Change in the WURSS-21-K total score (symptom score + quality of life score) from Baseline to Day 7
 
 
 
• Secondary Outcome Measures 
 
1. Change in the WURSS-21-K total score (symptom score + quality of life score) from Baseline to each time point (excluding Day 7)
 
2. Change in the WURSS-21-K symptom score from Baseline to each time point
 
3. Change in the WURSS-21-K quality of life score from Baseline to each time point
 
4. Change in the Nasal Congestion Severity Score from Baseline to each time point
 
5. Change in the Nasal Symptom Score VAS from Baseline to each time point
 
6. Change in the Systemic Symptom Score VAS from Baseline to each time point
 
 
 
 |

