#### **11.1.2. General Principles of Analysis**

- 1) All statistical analyses will be based on a two-sided test with a significance level ( $\alpha$ ) of 5%.
- 2) The statistical software SAS® Version 9.4 will be used for all analyses.

- 3) Continuous data will be presented as mean and 95% confidence interval, while categorical data will be presented as frequency and percentage.
- 4) If necessary, subgroup analysis will be conducted by categorizing subjects based on their baseline characteristics at the screening or baseline visit.

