### **11.3. Statistical Analysis of Safety Assessment**

The safety evaluation will analyze the frequency of adverse events and serious adverse events suspected to be related to the treatment. Adverse events will be collected through subject reports or investigator observations. The reported adverse events will be described narratively, and the frequencies of events related and unrelated to the study intervention will be recorded and presented using descriptive statistics. The event count per visit between the groups will be compared using Fisher's exact test. The pre- and post-treatment values for each laboratory test variable will be analyzed using a paired t-test to determine if there is a difference.

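### The only per-day contrast named for the daily scores is against baseline, which measures recovery from a cold and not GGTCS versus placebo; the laboratory and event-count tests in 11.3 also miss the arm comparison or the right unit

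*Protocol*

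**What the plan says.** The objective (section 4) is to compare efficacy and safety with placebo. The synopsis defines secondary endpoints 1 to 6 as changes from baseline to each time point. The first of them is "Change in the WURSS-21-K total score (symptom score + quality of life score) from Baseline to each time point (excluding Day 7").

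Three analyses bear on these scores:

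- Section 11.2.2(1) tests the change to Day 7 by the primary ANCOVA. It covers the nasal congestion score, the two VAS scores and the WURSS-21-K symptom and quality of life scores, among others. Section 11.2.1 gives that ANCOVA an adjusted difference between arms, a 95% confidence interval and a p-value.
- Section 11.2.2(2) uses a repeated-measures ANOVA to compare trends between the groups, "with Dunnett's procedure for multiple comparison correction (comparing each time point to baseline"). The synopsis says the same.
- The synopsis, but not 11.2.2, adds that "the pre- and post-treatment differences within each group will be analyzed using a Student's paired t-test".

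For safety, section 11.3 states: "The pre- and post-treatment values for each laboratory test variable will be analyzed using a paired t-test to determine if there is a difference". For adverse events it states: "The event count per visit between the groups will be compared using Fisher's exact test".

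**The concern.** The repeated-measures sentence has a between-group aim, but the contrast attached to it compares days with baseline. The text does not say whether this is done within each arm or pooled over arms; neither gives a treatment difference. Section 3 describes the cold as generally self-limiting, so a fall from baseline is expected on placebo. A reader of a table of day-versus-baseline p-values could take ordinary recovery for a drug effect.

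The gap is clearest for secondary endpoint 1. The WURSS-21-K total on days other than Day 7 is not listed in 11.2.2(1), so 11.2.2(2) is the only analysis that can cover it. The per-day result named there contains no comparison with placebo.

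The laboratory test has the same weakness: a pre/post difference cannot separate a drug effect from a change that also occurs on placebo. Fisher's exact test needs independent units, and one subject can contribute several events at a visit. An event count also has no natural non-event cell for the two-by-two table.

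**Working it through.** **Inputs.** From section 5.3: "the effect difference is set at 10 and the standard deviation at 21", two-sided 5%, 80% power, 70 evaluable and 88 enrolled per arm. From Table 1 in the same section: placebo change 29.09 (SD 21.89), n = 42, footnoted as adjusted for baseline.

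**The plan's own figure.** n per arm = 2(z₀.₉₇₅ + z₀.₈₀)² × 21² / 10² = 69.227 with unrounded quantiles, so 70. Then 70 / 0.8 = 87.5, so 88. Both reproduce, and power at 70 per arm is 80.4%. This size is for the between-arm comparison at Day 7.

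**Placebo against its own baseline, end of treatment.** t = mean change / (SD / √n):

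- n = 42: 29.09 / (21.89 / √42) = 29.09 / 3.378 = 8.61, p ≈ 1 × 10⁻¹⁰
- n = 70: 29.09 / 2.616 = 11.12, p ≈ 5 × 10⁻¹⁷
- n = 88: 29.09 / 2.333 = 12.47, p ≈ 5 × 10⁻²¹

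The unadjusted placebo means in Table 1 fall further, 66.48 − 33.33 = 33.15.

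**How small a placebo change would be significant.** At n = 70 and SD 21.89, any change above about 5.2 points is significant unadjusted. With Bonferroni over seven days, a conservative stand-in for Dunnett, the threshold is about 7.3 points.

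**Days before Day 7.** The protocol gives no daily figures, so a course must be assumed. A linear fall of 29.09 points over seven days gives 29.09 × d / 7: 4.2 points on Day 1, 8.3 on Day 2, 12.5 on Day 3 and 16.6 on Day 4. A simulation of 2,000 trials used two identical arms of 70, this course, SD of change 21.89 and within-subject correlation 0.5. The share of trials significant at 5% was:

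| Test, no treatment effect | Share significant |
|---|---|
| Placebo vs baseline, Day 1 (Bonferroni 7) | 13% |
| Placebo vs baseline, Day 2 | 66% |
| Placebo vs baseline, Day 3 | 97% |
| Placebo vs baseline, Days 4 to 7 | 99.95 to 100% |
| Group-by-day interaction | 5.4% |
| Day 7 change, between arms | 4.7% |

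The between-arm tests hold their 5% level. The contrast against baseline does not distinguish drug from placebo.

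**Laboratory values and adverse events.** The protocol gives no expected laboratory changes, event rates or numbers of repeat events, so no size can be computed. These points rest on what the named tests compare.

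**The case against.** The sentence in 11.2.2(2) opens with a between-group purpose. A repeated-measures ANOVA with that purpose implies a group-by-day test, and model terms and contrasts are often left to a statistical analysis plan, which is not shown here. Day 7 has a full between-arm ANCOVA. The within-group paired t-tests appear only in the synopsis, as an addition to that ANCOVA, and nothing presents them as evidence of efficacy. The t of 8.6 comes from an end-of-treatment change, not from daily data. The event-count wording may be loose phrasing for subjects with an event.

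Most of this stands, and it rules out several stronger readings that a reader might infer:

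- That the daily scores are never compared with placebo. The stated aim of the ANOVA and the Day 7 ANCOVA contradict this.
- That every daily test will be significant on placebo. Under the linear course Day 1 is significant in only 13% of trials, and Days 1 and 2 turn on an assumption.
- That the laboratory tests will look positive on placebo. The documents hold no laboratory data to show it.
- That the Fisher p-values are certain to be wrong. If no subject has more than one event at a visit, events and subjects coincide.

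The contrast itself does not fall under detail left for later. The protocol names one, and it does not serve the sentence's own aim. An omnibus interaction p-value gives no treatment difference on any day.

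**Conclusion.** The point holds for the secondary and safety analyses; the primary analysis is untouched. The one per-day contrast named cannot show a GGTCS effect on a given day. On the protocol's own placebo figures it would be significant without any drug effect by the end of treatment (t = 8.6 at n = 42, about 11 at 70 and 12.5 at 88). This takes 21.89 as the SD of individual changes and assumes a placebo response like that in Table 1. Significance from about Day 3 rests further on linear recovery and a within-subject correlation of 0.5. No between-arm contrast is named for Days 1 to 6, including all of secondary endpoint 1. For laboratory values the defect is that the only named test is pre/post, with no arm comparison. For adverse events it is that the named unit is the event and not the subject.

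**What to change.** - **Section 11.2.2(2) and the synopsis:** replace the Dunnett contrasts against baseline with the group-by-day test and the GGTCS-minus-placebo difference in change at each diary day. Take these from the repeated-measures model, adjusted for baseline, with 95% confidence intervals. Either adjust for multiplicity across days or label the per-day results as descriptive.
- **Synopsis:** label the within-group paired t-tests as descriptive.
- **Section 11.3, laboratory:** compare Visit 3 values between arms by ANCOVA on the screening value, for variables measured at both visits. Section 10.4 limits glucose to Visit 1, so it drops out.
- **Section 11.3, adverse events:** apply Fisher's exact test to the number of subjects with at least one event.

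All the data are already collected, so the cost is wording and slightly more analysis. Adjusted per-day intervals would be somewhat wider. Under Bonferroni over seven days the widening is about 1.4-fold, taking the ratio of the two thresholds above (7.25 / 5.22 = 1.39). Power for a 10-point difference on a single day, with SD 21 and 70 per arm, falls from 80% to 55%. A descriptive label avoids that loss but gives up formal claims for individual days.
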